### Participant, family, and school characteristics

Caregivers will report information about student age, gender, race and ethnicity, caregiver education, family composition, and academic support services received by students outside of school. School staff will report on students’ special education status, amount of special education services received, Section 504 services, and other services being provided to address student organizational problems. Publicly-available, online data about the free and reduced-price lunch percentage of each school will be accessed. A geo-mapping tool (Area Deprivation Index, ADI, [26]) will be used to determine each family’s neighborhood level of disadvantage; higher scores on this measure indicate greater disadvantage.

Medication and educational intervention status will be assessed at baseline and each assessment point by asking caregivers to indicate whether the child is currently on psychotropic medication, name of medication, and date of initiation. We will monitor change in medication status over the course of the intervention and follow-up periods. Caregivers will also be asked to indicate whether their child is receiving intervention (e.g., therapy, skills training, coaching) related to organizational skills/executive functioning.

Caregivers will report on their support of their child’s organizational skills related to materials management, homework management, and planning (i.e., how much time and support they provide to the child to maintain these skills).

The *Vanderbilt Rating Scales* will be used to assess severity of ADHD, oppositional defiant behavior, and internalizing symptoms. The caregiver- and teacher-report versions of the Vanderbilt scales will be used [27,28]. Informants rate how frequently each symptom occurs on a 4-point Likert scale (0 = never, 3 = very often). Both scales consist of a 9-item Inattention factor, a 9-item Hyperactivity-Impulsivity factor, an 8-item Opposition-Defiant factor, and a 7-item Internalizing factor. The internal consistency of each of these factors with middle school students has been shown to be high (>.90) [4].

HOPS providers, including school and research providers, will report on their professional roles, years of experience, gender, race and ethnicity, educational level, and years of experience. School providers will report aspects of the organizational (school) context that are relevant for the implementation of evidence-based practices in schools. The *Implementation Climate Scale* has 15 items; each item is rated on a five-point Likert scale (0 = not at all; 4 = very great extent). Higher scores indicate a more favorable climate. Research has supported the factor integrity and internal consistency of this scale [29].

### Measures of intervention implementation

#### Assessment of content and process fidelity.

The study team will video record intervention implementation for all 16 student sessions using a HIPPA compliant Outlook Teams meeting link; intervention providers will be asked to audio record each of the student sessions as a backup. Videotaped sessions determined to be key to intervention implementation because a new checklist is introduced (Sessions 2, 4, 8, 12), as well as the last self-management problem solving content session (Session 14) will be coded for each participant. In addition, one randomly selected session will be coded for each participant. In total, implementation fidelity will be coded for 6 of 16 student sessions (37.5%) to capture variations in implementation fidelity. Further, the study team will attempt to video record the caregiver and teacher sessions whenever possible, with intervention providers asked to audio record them as backup, and members of the research team will code a randomly selected subset of these sessions for fidelity. To evaluate the reliability of fidelity coding, a second, gold standard coder will double-code 25% of randomly selected, coded sessions**.**

The research team will evaluate content fidelity (treatment adherence) and process fidelity (intervention provider competence). Following the procedures used by [name] and colleagues in their RCT [4] but modified slightly to account for degree of implementation, content fidelity items will specify critical steps of the intervention and each item will be rated as a 0, 1, 2, or 3 (0 = not implemented; 1–2 = partially implemented; 3 = fully implemented). Scores on each item will be collapsed to indicate whether an item is implemented (2 or 3) or not implemented (0 or 1). In addition, scores will be recorded on a four-point scale to indicate the how well the intervention process was implemented. Process fidelity (competence) will be rated on a scale from 1 to 4 (1 = rarely; 4 = all or almost all of the time; adapted from Dumas et al. [30]). The process fidelity items will include those we have identified as important to organizational skills training interventions in our recent study of organizational skills in elementary school (e.g., using positive reinforcement for skill implementation, engaging student in practice and implementation planning, using a growth mindset rather than correction to provide feedback for skill use, individualizing content to student’s situation, and presenting key content clearly [8]). Process fidelity will be captured via two forms: Process Fidelity Form for HOPS Student Sessions and Process Fidelity Form for HOPS Caregiver/Teacher Sessions.

#### Assessment of intervention engagement.

Intervention providers will record student attendance at HOPS sessions and the duration of each session. The intervention provider will rate how involved the student was during and between sessions on a 6-point Likert scale (0 = not at all true to 5 = very true) (adapted from Chu & Kendall [31]). The average involvement score across sessions will be used as the index of student engagement. In addition, intervention providers will record caregiver attendance at caregiver consultation sessions. Using a measure developed by [name] and colleagues [4], and adapted by the current study team,the HOPS Study: Caregiver Engagement Rating Scale, the intervention provider will rate how engaged the caregiver was during each meeting using a scale similar to that used for students. Further, at the second caregiver meeting intervention providers will rate the extent to which the caregiver seems invested in implementing the monitoring and reward plan they had created using a 5-point Likert scale (1 = not at all to 5 = very much). A similar process is used to assess teacher engagement using the HOPS Study: Teacher Engagement Rating Scale. The reliability of these ratings will be determined by having study staff code the same student, caregiver, and teacher sessions that were selected for fidelity coding.

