### Importance of intervention implementation and relational processes

Intervention effectiveness depends to a substantial extent on how well the intervention is implemented (provider fidelity) and the extent to which participants are engaged or involved in the intervention [16,17]. Provider fidelity refers to adherence to the steps of the intervention curriculum as well as level of competence in providing intervention. Participant engagement includes attendance, active participation in sessions, and adherence to recommended intervention practices [16]. Another important implementation factor is the working alliance between the provider and student, or the ability of the provider to work with the student in a responsive, collaborative manner [18]. Monitoring implementation processes (provider fidelity, student and parent engagement) and assessing working alliance are especially important when interventions are provided under routine practice conditions, because there is less control over provider fidelity and often less emphasis on promoting intervention in a replicable, standardized manner. In this study, our team will carefully examine provider fidelity, student and parent engagement, and working alliance between the intervention provider and student participants and evaluate the extent to which these factors are associated with improvements in student outcomes.

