**Aim 1:** Evaluate the difference between HOPS-ST and TAU-WL on improvement in proximal outcomes (organization skills, homework performance) and distal outcomes (academic performance) at post-treatment (4-months after baseline) and explore the intervention’s sustainability (6 and 12-months after baseline). This aim will enable our team to determine the effectiveness of HOPS when provided by school professionals. We hypothesize that students in the HOPS-ST group will demonstrate significantly fewer OTMP skills deficits and homework problems and will show significantly better academic performance at post-treatment compared to students in TAU-WL. In addition, we expect the benefits of HOPS-ST to be maintained at follow-up.**Aim 2:** Examine the effectiveness of HOPS-RT in relation to TAU-WL. This aim will enable our team to replicate the findings of the [name] et al. [4] trial. We hypothesize that students in the HOPS-RT group will demonstrate significantly fewer OTMP skills deficits and homework problems and would show significantly better academic performance at post-treatment compared to students in TAU-WL. In addition, we expect the benefits of HOPS-ST to be maintained at follow-up.**Aim 3:** Explore differences in effect for HOPS-ST and HOPS-RT at post-treatment and follow-up.**Aim 4:** Explore mechanisms of action, specifically whether improvements in OTMP skills and homework performance mediate the effect of HOPS on improvements in academic performance.**Aim 5:** Explore whether student grade level, severity of organization problems, severity of ADHD, oppositional defiant behavior, and internalizing symptoms, and student medication status at baseline moderate the effect of HOPS on outcomes.**Aim 6:** Explore the extent to which treatment fidelity, student engagement, parent engagement, teacher engagement, and provider-student working alliance predicts outcomes for students in HOPS.**Aim 7:** Estimate the cost of providing HOPS under authentic practice conditions in schools.

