#### HOPS program.

HOPS includes 16 sessions with the student, each about 20 minutes long. HOPS has three components: (1) materials organization, (2) homework management, and (3) time management. In addition, the program includes two caregiver consultations and, when feasible, one teacher consultation to inform them how they can support implementation of HOPS strategies at home and school. In this study, HOPS will be implemented by a school provider or research provider. The school provider can be a teacher (general or special education) or member of the student support staff (e.g., school counselor, school psychologist). The research provider will be a member of the research team with experience in special education, school psychology, counseling, or education research.

***Materials Organization Component:*** Developing an efficient and structured system for managing school materials is a major goal of HOPS. During the first week of the program, students work with their provider to establish a system of backpack, binder, and computer files organization. An organization checklist, consisting of operationalized criteria for backpack, binder, and computer files organization is utilized. Baseline organization is recorded on the first session, and an organization system based on the checklist is established during the second session. The organization checklist is completed at every following intervention session during the program. Intervention providers work with students to develop strategies for maintaining their materials organization system.

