#### Analyses for Aim 6: Association of fidelity, engagement, working alliance to outcomes.

Our plan is to evaluate the extent to which provider intervention fidelity, student and caregiver engagement, and provider-student working alliance are associated with outcomes for participants in HOPS using multiple linear regression models. We will determine the proportion of variance in the outcome that is explained by the implementation factors, as assessed using adjusted R^2^ measures. Additionally, we will formally test the significance of the estimated coefficients to identify which implementation factor(s) are predictive of changes in the outcome measures.

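### The student engagement index leaves out attendance, which the protocol itself counts as part of engagement, and the Aim 6 regressions give attendance no role

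*Protocol article*

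**What the plan says.** Four places in the protocol article bear on this.

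- **Definition.** The background section on intervention implementation and relational processes states: "Participant engagement includes attendance, active participation in sessions, and adherence to recommended intervention practices".
- **Data collected.** Under Assessment of intervention engagement: "Intervention providers will record student attendance at HOPS sessions and the duration of each session". The same section adds: "The intervention provider will rate how involved the student was during and between sessions on a 6-point Likert scale".
- **Index.** That section then settles the summary: "The average involvement score across sessions will be used as the index of student engagement". It does not say whether the average is over sessions attended, held or planned, or how a missed session is scored.
- **Use.** Aim 6 reads: "Explore the extent to which treatment fidelity, student engagement, parent engagement, teacher engagement, and provider-student working alliance predicts outcomes for students in HOPS". The analysis section for Aim 6 will examine whether fidelity, "student and caregiver engagement, and provider-student working alliance are associated with outcomes for participants in HOPS using multiple linear regression models". No attendance or dose term is named there.

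The programme length is given under HOPS program: "HOPS includes 16 sessions with the student, each about 20 minutes long".

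**The concern.** Attendance is in the definition and in the data, but not in the index or the model. This is more than a detail left open. The article commits to one specific index, and that index is narrower than the construct it is named for.

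A provider can rate involvement during a session only if the session took place, so the average most naturally runs over attended sessions. On that reading, stopping early does not lower a student's score. A student who was keen for a few sessions and then left can score as high as one who completed the programme, or higher.

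The stake is how Aim 6 will be read. The Discussion counts the engagement assessment among the study's strengths and says that variation in effectiveness will be related to engagement. If Aim 6 found little association, a reader could not tell whether engagement matters little or whether the part of it that mattered was left out of the predictor.

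**Working it through.** The protocol gives no sample size, power or expected effect for Aim 6, so there is no planned figure to reproduce. The check compares two ways of averaging and then asks how much the choice could matter.

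**Inputs from the protocol:** 16 sessions; ratings from 0 to 5; 20 HOPS schools with an average of 4.5 students, so 20 × 4.5 = 90 students in Aim 6 before attrition. **Not in the protocol, hence assumed below:** the distribution of ratings, the rate and timing of early leaving, the involvement–attendance correlation, and how outcome depends on engagement.

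**Step 1. Two divisors.** For a student with k attended sessions and ratings r:

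- A = sum(r) / k (mean over attended sessions)
- B = sum(r) / 16 (missed sessions scored 0)

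| Student (assumed ratings) | A | B |
|---|---|---|
| 4 sessions, all rated 5 | 20/4 = 5.00 | 20/16 = 1.25 |
| 16 sessions, all rated 4 | 64/16 = 4.00 | 64/16 = 4.00 |
| 4 sessions, all rated 3 | 12/4 = 3.00 | 12/16 = 0.75 |

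Under A the first student ranks above the completer, and under B below. The third student ranks below the completer under both, so a reversal is possible but not automatic.

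It can also arise from fading enthusiasm alone. If ratings start at 5 and fall by 0.1 per session, stopping after session 4 gives 5 − 0.1 × 1.5 = 4.85, and completing gives 5 − 0.1 × 7.5 = 4.25. With a fall of 0.2 the values are 4.70 and 3.50.

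**Step 2. How often would an early leaver outscore a completer under A?** Simulation with assumed ratings of mean 3.5 and SD 0.8, limited to 0–5; 10% or 30% leave early after 2 to 12 sessions; the rest attend all 16.

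| Latent involvement–attendance correlation | Chance that a random leaver outscores a random completer |
|---|---|
| −0.3 | 0.64–0.66 |
| 0 | 0.50 |
| 0.3 | 0.33–0.36 |
| 0.6 | 0.18–0.22 |
| 0.8 | 0.08–0.11 |

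Under B the chance is at most about 0.07 throughout.

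**Step 3. Possible attenuation in Aim 6.** Assume that outcome correlates 0.40 with involvement summed over the 16 sessions, that early leavers attend 2–8 sessions and the others 13–16, and that n = 90. Power is for a single correlation by Fisher's z, two-sided 0.05. The summed measure itself would have R² = 0.16 and power 0.98. For index A:

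| Latent correlation | Early leavers 10% / 20% / 30%: r with outcome | Power |
|---|---|---|
| 0 | 0.28 / 0.23 / 0.19 | 0.75 / 0.57 / 0.44 |
| 0.3 | 0.31 / 0.27 / 0.25 | 0.85 / 0.74 / 0.67 |
| 0.6 | 0.34 / 0.32 / 0.30 | 0.90 / 0.86 / 0.83 |

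I reran this table; it is stable to about 0.01. R² for index A runs from 0.04 to 0.11. Entering sessions attended beside mean involvement gives 0.15–0.16 in every row.

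**Step 4. The converse.** If outcome instead follows mean involvement with correlation 0.40, index A loses nothing and B loses the same amount: 0.28, 0.23 and 0.19 in the zero-correlation case. Step 3 therefore does not show that a summed index is better. It shows that a single index of either kind can miss something, and that two terms guard against both cases.

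**The case against.** The strongest reply is that separating quality of involvement from quantity of sessions is ordinary measurement practice. The definition is in the background and does not demand one composite score. Attendance is recorded as its own variable, the rating of involvement between sessions plausibly covers adherence, and the Aim 6 text names kinds of predictor, not a closed list. The divisor and exact model terms are the sort of detail a full protocol or analysis plan may hold.

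Much of this stands. An unstated divisor would be no finding on its own, and mean involvement is a legitimate measure of participation. What remains is that the article names this average as the index of student engagement and gives attendance no analytic role, although its own definition includes it.

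Two stronger readings are tempting, and the document supports neither. A reader might infer that the index misranks exposure to HOPS; but it is offered as a measure of engagement, and nowhere as a measure of dose. A reader might also infer that the Aim 6 association would be reversed; but every correlation in the simulation is positive, and individual reversals become uncommon if involved students also attend more.

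It is also fair to object to scoring missed sessions as 0. The Discussion describes limited school capacity to deliver HOPS, so a session may be missed for reasons that have nothing to do with the student. Zeros would mix non-delivery into student engagement, possibly to a different degree for school and research providers. That objection stands and shapes the fix.

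**Conclusion.** The point holds in a limited form. The student engagement index omits the attendance component of the protocol's own definition, and Aim 6 does not bring it back. If the mean is over attended sessions, an early leaver can score as high as or higher than a completer, and a weak association in Aim 6 could partly reflect that omission.

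The size is not known. Under the assumptions of Step 3, a correlation of 0.40 would appear as 0.34 to 0.19; if outcome depends on quality of involvement alone, there is no loss. The deciding quantities are the rate of early leaving, the involvement–attendance correlation and whether outcome depends on cumulative involvement, and the protocol gives none of them.

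The consequence is confined to Aim 6, which is exploratory. The intent-to-treat comparisons of Aims 1 to 3 do not use the index.

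**What to change.** - **Assessment of intervention engagement:** state that mean involvement is taken over attended sessions, and describe it as the participation part of student engagement. Do not score missed sessions as 0 in the primary index.
- **Analyses for Aim 6:** add the number of sessions attended, out of 16, as a separate student-engagement predictor beside mean involvement, and report both coefficients.

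This is a change of wording. Attendance and per-session ratings are already being recorded, so nothing new has to be collected. The cost is one more predictor, and so one degree of freedom, in an exploratory model of about 90 students. Sessions attended will still include some missed for school or provider reasons, so its coefficient should be read with that in mind; keeping it separate leaves mean involvement free of that mixture.

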### Measures of acceptability, usability, working alliance, and cost

Caregiver acceptability will be assessed using a 13-item caregiver satisfaction measure developed for use with HOPS [32]. The *Children’s Intervention Rating Profile (CIRP),* a 7-item measure, will be adapted to assess student views of acceptability [33]. Intervention provider (both school provider and research provider) usability will be examined by the *Usage Rating Profile–Intervention–Revised (URP-IR),* a 29-item measure assessing factors influencing the usage of school interventions [34]. The URP-IR will only be completed once by each provider.

The working relationship between the intervention provider and student will be assessed at the end of intervention using an adaptation of the *Working Alliance Inventory-Short Version* (WAI-S; [35]). The WAI-S consists of 12 items rated on a 7-point Likert scale (1 = never; 7 = always) assessing agreement on tasks and goals and the student-provider bond); higher scores are more favorable. The internal consistency (alpha coefficient) of this measure among middle school students was demonstrated to be.92 for intervention providers and.90 for students. In previous research, scores on the WAI-S have been shown to be associated with intervention outcomes [11]. The WAI-S will be filled out by the student (“Working Alliance Inventory-Student”) and intervention provider (“Working Alliance Inventory-Counselor”).

Total costs (labor and non-labor) associated with the implementation of HOPS as well as training and technical assistance for providers in each school will be calculated according to the ingredients method [36]. To do so, we will document intervention implementation activities of providers, trainers, and project assistants using time diaries, administrative records, and interviews. We will conduct time use interviews with providers at the end of each intervention period. Materials costs will be determined using acquisition costs. The costs then will be determined from the total effort on each activity and per hour wage rate of the person conducting the activity using local price levels (average salary and benefits for those in job categories matching the staff providing services). Costs for HOPS will include: (a) time to establish and maintain the relationship with each school, (b) time spent conducting the initial training for providers; (c) provider time spent implementing each student, parent, and teacher session, (d) time spent providing technical support to each provider, and (e) materials costs. We will distinguish two types of costs: cost of physical materials used for training and interventions (e.g., training manual for each provider) and costs associated with time spent for training, technical support, and intervention implementation [37]. In addition, costs for initial training and tech support of providers will be differentiated from the ongoing costs of implementation to provide separate estimates of costs for start-up in each school and costs for ongoing implementation. Cost estimates will not include time and materials needed for research activities (e.g., participant recruitment and enrollment, data collection).

Intervention, training, and technical support time will be derived from administrative records of HOPS sessions, diaries completed by [name] and technical support assistants, and training website usage data. Study staff will interview intervention providers (both school providers and research providers) after intervention to assess their experience delivering the intervention, including how much time they have spent on session preparation, delivery, and follow-up.

